#### Moderators

Differential effects of treatment on the outcomes associated with characteristics of the mothers and daughters (ie, demographics, political ideology, skin cancer history, and skin phenotype [83]) and their relationship (maternal communication and relationship quality [84-86]) will be tested using multiple group SEM (for categorical characteristics) and a treatment by characteristic interaction term (for continuous characteristics). All moderators will be level 1 variables. Tests of moderation will be built on top of the multilevel models with latent variables described above. A Holm-Bonferroni correction will be applied to adjust for multiple exploratory tests. These effects, tested in secondary analyses, will need to be large in order for a significant effect to be detected.

#### Mediators

Theorized mediators (ie, indoor tanning intentions, attitudes toward indoor tanning [73,87-89], conditional perceived susceptibility to skin damage [90], self-efficacy to resistant indoor requests, and mother-daughter indoor tanning–specific communication) and campaign engagement (level 1 variables) from the 6-month follow-up will be regressed on the treatment indicator (a level 2 variable) in a multilevel SEM. If treatment effects on mediators emerge, a full multilevel SEM with direct and indirect effects on the primary outcomes of IT permissiveness and behavior will be assessed using a causal mediation framework [91,92]. A bootstrap resampling procedure will be used to construct 95% confidence intervals around each indirect effect estimate [93,94].

#### Seasonality Issues

In order to account for the issue of seasonality (ie, that indoor tanning is more common during certain times of the year), we will measure indoor tanning at each follow-up, asking specifically about tanning during the months of December-March. We will also include date of measurement as a covariate.  We will control for month of assessment and number of months that have elapsed since baseline. In addition, the treatment and control group, randomized together, will be surveyed at precisely the same times to ensure equivalency.

## Results

The first wave of the intervention began in September 2016. We anticipate on continuing recruitment through October 2018 and completing this study by October 2019. Results will be examined at that time.

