**Methods:**

The study is a 12-month randomized controlled trial comparing 2 conditions: an attention control Facebook private group where content will be relevant to teen health with 25% focused on prescription drug abuse, a topic unrelated to tanning; and the intervention condition will enter participants into a Facebook private group where 25% of the teen health content will be focused on indoor tanning. A cohort of 2000 mother-teen daughter dyads will be recruited to participate in this study. Only mothers will participate in the Facebook groups. Both mothers and daughters will complete measures at baseline, end of intervention (1-year) and 6 months post-intervention. Primary outcomes include mothers’ permissiveness regarding their teenage daughters’ use of indoor tanning, teenage daughters’ perception of their mothers’ permissiveness, and indoor tanning by both mothers and daughters.

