**Results:**

The first dyad was enrolled on March 31, 2016, and we anticipate completing this study by October 2019.

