### Study Design

The study design is a randomized controlled trial comparing 2 conditions over 1 year (Figure 1). Participants will be recruited in waves of approximately 84 and then randomized into the intervention or control condition. We continue in this way until a total of 25 waves have been enrolled, producing 25 groups in the intervention condition and 25 groups in the control condition each with approximately 42 participants. Participants will be blinded to condition and assessment points will occur at baseline, end of intervention (1-year), and 6 months postintervention.

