### Recruitment

Mother-daughter dyads will be recruited across 40 counties in east Tennessee using two primary strategies: (1) Coordinated School Health (CSH) Coordinators in each school system will provide access to mothers and daughters in high schools, and (2) study staff will recruit mothers and daughters through partnerships with community-based organizations (eg, churches, sports leagues, clubs, health clinics, etc). A local Expert Advisory Board, made up of regional CSH Coordinators, public health educators, and maternal and child health professionals is providing insight into effective community-based recruitment. CSH, which is housed in the Tennessee Department of Education, has the mission of working with schools and parents to improve children’s health, making them a natural partner in this effort. CSH Coordinators are asked to send study invitations to mothers through their normal channels (eg, back-to-school packets, flyers with report cards, email, newsletters, etc). Access to families through schools can be challenging, but partnering with CSH ensures we will not interfere with time, curricular, and other constraints. Schools that assist with mother-daughter recruitment will receive a US $200 mini-grant for CSH-related program materials. At the same time, study staff will systematically canvass communities across the region, beginning in the far northeast corner of the state and working their way south and west to partner with local organizations, media outlets, and employers to advertise the study to mothers and teen daughters in the region. We chose multiple recruitment methods based on our past experience recruiting women and adolescent girls in this hard-to-reach population [46]. CSH Coordinators and community-based organizations often have direct access to mothers of high school students and can serve as credible recruiters. For eligible participants, we expect a refusal rate of 30%, based on our previous experiences in this population [46].

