#### Content

All participants will be invited to private Facebook groups to participate in the *Health Chat* program. The privacy setting in these groups is set to “secret” to prevent members and content of the group being visible to the public, including other Facebook users. Members of a private group with a “secret” privacy setting can only see information in each other’s profiles as indicated by their personal privacy settings. Members must also be invited to the group by the group administrator who will be a study staff member. The content of *Health Chat* is tailored to mothers and although only mothers will be in the Facebook groups, they will be encouraged to share content with their daughters. Posts will occur twice daily for 12 months for a total of 720 posts. Mothers will be encouraged to contribute their own content to the Facebook group via comments, original posts to share opinions or pose questions, and participation in group activities. Each group will be hosted by a community manager who will oversee the editorial calendar, maintain the feed, stimulate engagement, and monitor the broader media environment to discover trending topics and new research findings to post.

Our preliminary focus groups of mothers and key informant interviews of CSH coordinators revealed greater interest in a Facebook group focused broadly on health as opposed to a single topic like indoor tanning. For this reason, the *Health Chat* program will address health topics identified as of high interest by our focus group participants and CSH coordinators. These topics include healthy lifestyle, mental health, mother-daughter communication, and substance use. An advisory board of experts on these health topics provided evidence-based protocols and resources, which were then converted to Facebook posts by our team. In the *Health Chat* feed, 80% of posts were developed in advance based on evidence-based interventions and resources while 20% of posts will be pulled from emerging research and current events (eg, news reports of new tanning legislation, public service announcements about the health topic) relevant to the health topics.

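### Recruiting through October 2018 and completing by October 2019 leaves 12 months for an 18-month follow-up; the dates fit only a 6- and 12-month schedule that the study design contradicts

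*Protocol article*

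**What the plan says.** The article gives the assessment times in two places. Abstract, Methods: "Both mothers and daughters will complete measures at baseline, end of intervention (1-year) and 6 months post-intervention". Study Design: "assessment points will occur at baseline, end of intervention (1-year), and 6 months postintervention". The Content section confirms the intervention length: "Posts will occur twice daily for 12 months". On these passages each wave is assessed at months 0, 12 and 18.

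The calendar is also given twice. Results section: "We anticipate on continuing recruitment through October 2018 and completing this study by October 2019". It adds that the first wave began in September 2016 and that results are to be examined at completion. Abstract, Results: "The first dyad was enrolled on March 31, 2016, and we anticipate completing this study by October 2019".

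Two other sections use different follow-up times. Sample Size and Power Calculations allows for 20% loss at 6 months and 30% by 12 months, and counts 1680 and 1470 assessed in each sample at a 6-month and a 12-month follow-up. Mediators takes its mediator values from a 6-month follow-up. The schedule in the Abstract and Study Design has no 6-month visit after baseline.

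Under Primary Outcomes, permissiveness, tanning behavior and intentions are measured at baseline and both follow-ups, and mothers are asked about support for bans at the final one.

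**The concern.** Only 12 months separate the end of recruitment from completion, while the stated design needs 18 months per wave. The last recruits would just reach the end of their intervention when the study is declared complete and its results are examined.

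If the dates were held, the latest waves would have no final follow-up. Every outcome due at that visit would be missing for them. The missing waves would be the latest in calendar time, which matters because the Seasonality Issues section treats December to March as the period of special interest. The planned allowance for loss covers individual dropout to 12 months, not the absence of whole waves.

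**Working it through.** **Inputs.** Recruitment ends October 2018, completion is October 2019 and the first wave began in September 2016 (Results). First enrolment was 31 March 2016 (Abstract, Results). There are 25 waves of about 84, each forming one intervention and one control group of about 42 (Study Design). Power inputs are two-sided alpha 0.05, d=0.50, ICC 0.05 and 50 groups of 25 (Sample Size and Power Calculations).

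**Step 1: can the stated completion date be reproduced?**
- Months 0/12/18: October 2018 + 12 + 6 months = April 2020. The stated date is 18 − 12 = 6 months short (5 to 7, depending on whether the start or end of October is meant).
- Months 0/6/12: October 2018 + 12 months = October 2019. This reproduces the stated date, with no slack.

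**Step 2: are the sample-size figures tied to one schedule?** 25 × 84 = 2100; 2100 × 0.80 = 1680; 2100 × 0.70 = 1470; 1470 × 0.85 = 1249.5, or about 1250. All reproduce, on follow-ups labelled 6 and 12 months. So the sample-size section and the calendar agree with each other, and both disagree with the Abstract and Study Design.

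**Step 3: which waves would be affected if month 18 and October 2019 both stood?** October 2019 − 18 months = April 2018, so waves starting after about April 2018 are late. The article has no wave calendar; I assume 25 evenly spaced starts.
- From September 2016 to October 2018: 6/25 months = 24%, or 6 waves, 6 × 84 = 504 dyads. Starts to the beginning of October 2018 with completion at the end of October 2019 give 5 waves, 420 dyads.
- From 31 March 2016 to the end of October 2018: 6/31 months = 19%, or 5 waves, 420 dyads.
- Over all start- and end-of-month readings: 17% to 27%, 4 to 7 waves, 336 to 588 dyads.
- Sensitivity: the first wave began about 5 months after the first enrolment. If the last waves start 1 to 5 months after recruitment closes, 7 to 9 waves miss month 18 and 1 to 4 also miss month 12.

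**Step 4: what would that cost in power?** With J groups of n mothers, SE(d) = √{4[ICC + (1 − ICC)/n]/J}, tested on t with J − 2 degrees of freedom.
- Planned, J=50, n=25: SE = √(4 × 0.088/50) = 0.084. Power at d=0.50 is above 0.999, consistent with the article's claim to far exceed 0.80. Minimum detectable d at 80% power is 0.24.
- Without 5 or 6 waves, J=40 or 38, n=25: power at d=0.50 is 0.999. Minimum detectable d is 0.27 or 0.28.
- At n=42, before any attrition: minimum detectable d goes from 0.22 (J=50) to 0.25 (J=40 or 38).

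The n=25 figures are already net of the 30% loss and the 15% minority allowance.

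**Step 5: season.** Starts from May to October 2018 have month-18 surveys from November 2019 to April 2020. If waves start monthly from September 2016, month-18 surveys run from March 2018 to April 2020. Nine of those months lie in December to March: one in March 2018, four in 2018–19 and four in 2019–20. The four in 2019–20 would be lost.

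**The case against.** The strongest reply is that the dates may be right and the assessment times wrong. October 2019 matches the 6- and 12-month schedule exactly, and the sample size is built on it. This stands to the extent that the article does not show which element is in error, so month 18 cannot be treated as settled. It does not remove the contradiction, because the Abstract and Study Design both put the last visit 6 months after the intervention.

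Second, the dates are anticipated. Nothing says follow-up stops in October 2019 or that late waves are dropped, so the likelier outcome may be a late finish. That also stands, and it makes the loss of waves conditional. The mismatch remains, since the completion date appears twice and fixes when results are examined.

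A reader might go further and infer three things that the article does not support.
- *A known fraction of waves cannot supply the final outcome.* The fraction rests on assumed even spacing and on the date being enforced.
- *The trial would be underpowered or biased.* Power at the planned effect is essentially unchanged. Both arms of a wave are randomized together and surveyed at the same times, so a lost wave removes both arms equally.
- *The loss would be geographic.* Staff canvassing is described as "beginning in the far northeast corner of the state and working their way south and west", but school-based recruitment runs in parallel with no stated geographic order. A geographic pattern is possible, not established.

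**Conclusion.** The contradiction holds. Under months 0, 12 and 18, the last wave's final survey falls at about April 2020, six months after stated completion. That gap follows from the article's own dates and needs no assumption beyond the reading of October. The documents do not settle whether the dates or the assessment times are wrong.

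The consequence is conditional. If month 18 stands and October 2019 is enforced, about 5 to 6 of 25 waves (range 4 to 7, assuming even spacing and starts no later than October 2018) would lack the final follow-up. Their month-12 outcomes would just fit. The price is a modest loss of precision and one December-to-March season at the final follow-up. It is not a power failure at d=0.50, nor by itself a biased comparison.

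**What to change.** State one assessment schedule and use it in the Abstract, Study Design, Sample Size and Power Calculations, and Mediators. Changing the completion date alone would leave the 6- and 12-month follow-ups in the last two sections contradicting the first two.

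If month 18 is kept, either restate completion and final analysis as no earlier than about April 2020, or close recruitment by about April 2018 so that all 25 waves can reach month 18 by October 2019. Restate the expected loss to follow-up for the visits actually planned. If waves may start some months after recruitment closes, count from the last wave's start.

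In either case, say that the final-follow-up analysis will not be run until the last wave's survey has closed.

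The cost is a text change, plus either a completion date about six months later or the same 25 waves recruited at a faster rate.

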## Discussion

### Mothers as a Key Intervention Target

The proposed research will fill 2 gaps in the existing literature by (1) decreasing mothers’ permissiveness to allow their daughters to tan so as to maximize public policy on indoor tanning, and (2) using social media to deliver a health communication campaign targeting mothers. Past research on indoor tanning policy has examined industry compliance and policy impact on mothers and daughters [29,30,95-109], but has not evaluated health communication interventions to maximize the impact of indoor tanning policy. Studies of policy interventions on sun safety of youth in general are rare, limited to a few studies on policy adoption by US and Australian schools [110,111] (including a successful intervention by our team [112]) and recreation centers [113,114].

### Advantages of Social Media as Intervention Modality

Social media has revolutionized communications and offers several advantages for an indoor tanning campaign. Social media can reach many across the United States, including mothers [115], because most US adults use the Internet and social media [115]. Use is especially high by women (72% are on Facebook, 25% on Pinterest, 16% on Instagram, and 15% on Twitter) [115]. Further, most US adults (80%) use the Internet to retrieve health information [116] because it is low-cost, available 24/7, private [117], can be personalized, and enhances social connections [118]. At least 20% of women aged 25-44 use social media to post about their health and share health videos/images [119-121]. Social media users create and share content that provides opportunity for information dissemination, social norm change, and broad impact [122,123]. Health is a popular topic on social media as indicated by the formation of patient communities and health-related hashtags [119-122,124]. A 2011 survey found that 34% of Internet users had read a commentary or experience about health/medical issues on a website or blog [125]. Social media can also stimulate collective action [112,126]. Social media has been at the forefront of large collective political actions, including oppositional movements in Egypt, Occupy Wall Street, the Tea Party [127], and the Obama presidential campaign (which had 32 million Facebook friends, 22 million Twitter followers [128], and 300 million YouTube views [129], and digitally raised US $525 million) [127]. Social media can also heighten awareness, frame issues, develop/expand networks, and motivate Web-based and offline collective actions (eg, writing letters, organizing meet-ups, attending hearings/events, registering to vote, and sharing information [112,126,130-132]). For example, an organ donor registration effort by Facebook in 2012, yielded 13,054 new registrations in its first day (21.1 times more than an average day) [133]. The proposed indoor tanning social media campaign is intended to change attitudes about indoor tanning and ultimately, elevate support for stricter, more effective bans on minors’ access to indoor tanning facilities. Currently, very few studies have been published on social media in public health campaigns, so the proposed project will also fulfill calls by National Institutes of Health for research to identify best practices for using social media and Web 2.0 technologies in health behavior interventions. Social media interventions are not without limitations. One challenge is that frequency of social media use varies across individuals with some people logging in several times per day and others logging in once per week or less. Nonusers and infrequent users may be less likely to benefit from social media–delivered interventions, unless they are convinced to engage. In the present study, we will conduct a year-long campaign of twice daily posts to provide numerous opportunities for participants to see the content. We will also employ social media marketing strategies to encourage engagement. We will also study engagement patterns by user characteristics to inform the nascent, but much needed literature on engagement in social media interventions [134].

Many federal and state agencies, nonprofits, and health care providers already use social media extensively to disseminate information [135,136] (eg, National Institute on Drug Abuse, CDC, and Environmental Protection Agency), and also use generated video contests to reach young people on immunization [137], tobacco [138], organ donation [139], and HPV vaccine [137,140]. The indoor tanning industry also actively markets its services on social media [141]. Thus, the results of this trial will deliver social media content grounded in theory, and test it in a randomized design with state-of-the-art measures. Also, they will contribute much needed insights on how to employ social media for health behavior change and disease prevention both for indoor tanning and other health risk behaviors and inform future social media efforts by public health and health care organizations.

## Appendix

Multimedia Appendix 1 Summary sheets from grant review.

## Abbreviations

CDC: Centers for Disease Control
FDA: Food and Drug Administration
CSH: coordinated school health
DIT: diffusion of innovations theory
HPV: human papillomavirus
SCT: social cognitive theory
SEM: structural equation model
TT: transportation theory
